## 19.2 Relationship to study drug

The investigator or a medically qualified sub-investigator will review each event and assess its relationship to the study drug based on available information according to the following guidelines:

- Definite: A reaction that follows a distinct temporal relationship from administration of the study drug; that follows a known reaction to the agent or chemical group of the study drug; and that cannot be explained by the subject's clinical state or other factors.
- Probable: A reaction that follows a reasonable temporal sequence from administration of the study drug; that follows a known or expected response pattern to the suspected study drug; and that could not be reasonably explained by the known characteristics of that subject's clinical state.
- Possible: A reaction that follows a reasonable temporal sequence from administration of the study drug; that follows a known or expected response pattern to the suspected study drug; but that could readily have been produced by a number of other factors.
- Unlikely: A reaction that does not follow a reasonable temporal sequence from administration of the study drug; however, causality from the study drug cannot be ruled out.
- Unrelated: A reaction for which sufficient data exist to indicate that the etiology is unrelated to the study drug.

For the purpose of expedited SAE regulatory reporting obligations (i.e., to regulatory authority and IEC, events assessed by the investigator as definitely, probably, or possibly related to study drug will be considered "related" to study drug (i.e., associated with the use of study drug). Events assessed as unlikely or unrelated will be considered "not related" to study drug (i.e., not associated with the use of study drug).

|  |  |                    |                |
|--|--|--------------------|----------------|
|  |  | CRS Study No.:     | 090/18-03.MT   |
|  |  | Sponsor Study No.: | AT1001-035     |
|  |  | EudraCT No.:       | 2018-003684-57 |

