### Safety and tolerability

The most common adverse reaction in clinical studies was headache, which was experienced by approximately 10% of patients who received migalastat.

Very common adverse reactions ( $\geq 1/10$ ) were: abdominal pain, diarrhoea, nausea, fatigue, pain, dizziness and headache.

Common adverse reactions ( $\geq 1/100$ ,  $< 1/10$ ) were: rash and pruritus.

 Updated in consistency with update of Investigator's Brochure (Version 17)  
Integrated Clinical Study Protocol, Final 3.0, 29 Aug 2019

In clinical studies, to date, 3 serious adverse events (SAEs) considered possibly related to migalastat have been reported: fatigue and paresthesia in one subject and proteinuria in one subject.

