#### **19.4.3 Additional Reporting Requirements for Suspected Unexpected Serious Adverse Reactions**

Amicus is responsible for processing suspected unexpected serious adverse reactions (SUSARs). SUSARs are also referred to as alert reports, expedited safety reports, and IND safety reports.

A SUSAR is defined as any SAE that is determined to be associated with the use of study drug and is unexpected (not currently listed in the safety reference information [see migalastat IB] or is not listed at the specificity or severity that has been observed). Amicus will notify all investigators currently conducting migalastat clinical studies of all SUSARs in accordance with applicable regulations. Suspected unexpected serious adverse reactions will be reported to the regulatory authority and IEC according to the rules in effect in each country where study sites are located:

- If the SUSAR is fatal or life-threatening, regulatory authorities and ethics committees will be notified within 7 calendar days after Amicus learns of the event.
- If the SUSAR is not fatal or life-threatening, regulatory authorities and ethics committees will be notified within 15 calendar days after Amicus learns of the event.

These notifications will need to be filed in the site's Study File Notebook and submitted to the site's IEC in accordance with policy.

Safety updates will be provided periodically to the regulatory authority and IEC responsible for the study according to the rules in effect in Germany. These updates will include information on SUSARs and other relevant safety findings.

|  |  |                    |                |
|--|--|--------------------|----------------|
|  |  | CRS Study No.:     | 090/18-03.MT   |
|  |  | Sponsor Study No.: | AT1001-035     |
|  |  | EudraCT No.:       | 2018-003684-57 |

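### Section 19.2 ties every related causality grade to a known or expected reaction, so a new type of reaction fits no grade and cannot meet the SUSAR definition as written

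*Protocol*

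**What the plan says.** Section 19.2 of the Protocol gives five causality grades. Definite asks for a reaction "that follows a known reaction to the agent or chemical group of the study drug". Probable asks for one "that follows a known or expected response pattern to the suspected study drug; and that could not be reasonably explained" by the subject's clinical state. Possible asks for one "that follows a known or expected response pattern to the suspected study drug; but that could readily have been produced by a number of other" causes. In each of these three grades the pattern condition stands beside a timing condition and a condition on other explanations, and all three have to be met.

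The two remaining grades work differently. Unlikely is "A reaction that does not follow a reasonable temporal sequence from administration of the study drug", with the rider that causality is not excluded. Unrelated needs enough data to show that the cause lies elsewhere.

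For expedited reporting, Section 19.2 counts Definite, Probable and Possible, as graded by the investigator, as related, and explains related as meaning associated with use of the drug. Unlikely and Unrelated count as not related. Section 19.4.3 then defines a SUSAR as "any SAE that is determined to be associated with the use of study drug and is unexpected". Unexpected there means absent from the safety reference information in the Investigator's Brochure (IB), or not listed in it at the severity or specificity observed. Section 9.7.1.5 also uses the grades, because the frequency tables of treatment-emergent adverse events (TEAEs) are split by relationship to the drug.

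**The concern.** Causality and expectedness are two separate questions: did the drug plausibly cause the event, and was that kind of event already known? A SUSAR is the case where the answers are yes and no. Section 19.2 makes a yes to the first question depend on the event already being known or expected, which works against the definition in Section 19.4.3.

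This matters because safety and tolerability form the secondary objective, and Section 7.3 states that migalastat has no prior study in dialysis subjects. A reaction of a type not seen before is one of the things that a first study in a population should be able to label correctly. At stake are the classification of such an event for onward reporting to authorities and ethics committees, and its place in the TEAE tables by relationship.

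**Working it through.** No figure in the plan is involved, so the check is a logical one: apply the written criteria to a test event.

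**Test event.** Serious; new in type (not known for migalastat or its chemical group, and not otherwise expected); plausibly timed after dosing; no proven other cause.

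**Step 1: the five grades in Section 19.2.**

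| Grade | Condition that decides | Met by the test event? |
|---|---|---|
| Definite | reaction known for the drug or its chemical group | No |
| Probable | pattern known or expected for the drug | No |
| Possible | pattern known or expected for the drug | No |
| Unlikely | timing not plausible | No, the timing is plausible |
| Unrelated | data showing another cause | No, there are none |

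Result: 0 of 5 grades fit, and 0 of the 3 related grades can be reached.

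**Step 2: carry this into the SUSAR definition.**

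- SUSAR = serious AND associated AND unexpected (Section 19.4.3).
- Associated = graded Definite, Probable or Possible by the investigator (Section 19.2).
- Each of those three grades implies a known or expected reaction (step 1).
- The test event is serious and unexpected, but not associated. It is therefore not a SUSAR.

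Section 19.4.3 puts the determination of association in the passive and does not say who makes it. Section 19.2, however, ties relatedness for expedited reporting to the investigator's grade. The Protocol describes no separate sponsor assessment of causality and no default for an event that fits no grade.

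**Step 3: which SUSARs remain possible.** The pattern condition in Section 19.2 (known or expected) is not the same as listing in the IB (Section 19.4.3). So two routes stay open:

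- a listed reaction seen at greater severity or specificity than listed;
- a reaction known for the chemical group, or otherwise expected, but not listed in the IB.

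Neither is a new type of reaction.

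**Step 4: repeat step 1 with the pattern condition removed from Possible and made supportive in Probable and Definite.**

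- If other factors could readily explain the test event, it meets Possible (plausible timing, other explanations available).
- If the subject's clinical state does not reasonably explain it, it can meet Probable (plausible timing, no such explanation).

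In both cases the event is related, hence associated. Being unexpected as well, it meets the SUSAR definition, and Sections 19.2 and 19.4.3 agree.

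**The case against.** **The grades are guidance.** Section 19.2 calls them guidelines, whereas Section 19.3 tells the investigator to use definitions for severity. An investigator could choose Possible on medical judgement. This stands as a limit: the finding describes the written criteria, not necessarily practice. But the Protocol gives no other rule, so the right result would depend on departing from the text.

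**A new event would not be lost.** Every SAE goes to the sponsor within 24 h whatever its grade (Section 19.4.2). All adverse events are listed individually, and TEAEs are also tabulated by system organ class and preferred term (Section 9.7.1.5). With 12 planned subjects each event is visible. The first ESRD subject's safety data are discussed before the others are treated (Section 9.1), and periodic safety updates go beyond SUSARs (Section 19.4.3). All of this stands. It confines the gap to classification and leaves detection intact.

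**The event is not classed as not related.** A reader might infer that the text sends a new reaction to Unlikely or Unrelated and so out of expedited reporting. The text does not do that. Its conditions for those two grades are not met either, and nothing steers the site to them over Possible. As written, the event has no grade.

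**SUSARs are not confined to worse forms of listed reactions.** A reader might infer this too, but the second route in step 3 of the working shows otherwise.

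**Conclusion.** The point holds in a limited form and should be fixed. All 3 related grades carry a known or expected condition, 0 of 5 grades fit a new and plausibly timed reaction, and Sections 19.2 and 19.4.3 cannot both be applied literally to such an event. What is affected is classification for onward expedited reporting and the TEAE tables by relationship. The primary pharmacokinetic endpoints are untouched.

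This rests on reading the three conditions in each related grade as cumulative, which is how they are joined, and on no document outside the Protocol supplying a separate causality rule. The eCRF Completion Guidelines and the sponsor's safety procedures were not available.

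Three further readings are tempting but not supported:

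- **Higher exposure makes new reactions likely here.** The Protocol reports a 4.3-fold rise in AUC with similar Cmax in severe impairment (Section 7.4), but gives no exposure figure for ESRD and predicts that the drug is dialyzable (Section 7.3). The point does not need this argument.
- **The adverse reactions named in Section 7.2 mark the limit of what is known.** They are a summary. Expectedness is judged against the IB, which is not at hand. The paresthesia and proteinuria mentioned there were considered possibly related, so they are known events and do not illustrate the gap.
- **Unlikely should count as related because causality is not excluded.** That grade concerns events with implausible timing, a different case. Where to draw that line is a matter of preference.

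**What to change.** In Section 19.2:

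- **Possible:** delete the condition that the event follow a known or expected pattern. Keep plausible timing and the availability of other explanations.
- **Probable and Definite:** keep the known pattern as a feature that supports the grade, and state that it is not required.
- **Add one sentence:** causality is graded without regard to whether the reaction is already known or listed; expectedness is judged separately under Section 19.4.3.

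Section 19.4.3 can stay as it is. Bring the eCRF Completion Guidelines into line if they repeat the grades.

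The cost is a wording change, with no new data, visits or subjects. A few more events may be graded Possible; the documents give no basis for a number.

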### 19.3 Severity assessment

The investigator or a qualified sub-investigator will review each event and use the following definitions for rating intensity:

- Mild: Awareness of sign, symptom or event, but the AE is easily tolerated and does not interfere with daily activity.
- Moderate: Discomfort enough to cause interference with usual activity and may warrant intervention, but the subject is still able to function.
- Severe: Incapacitating with inability to do usual activities or significantly affects clinical status, and requires medical intervention.

It is important to distinguish the difference between events that meet the definition of serious and events that are deemed as severe in intensity. AEs assessed as severe in intensity are not SAEs unless at least 1 of the outcomes in [Section 19.1.2](#) occurs. An AE of any intensity must be reported as an SAE if at least 1 outcome in [Section 19.1.2](#) occurs.

### 19.4 Reporting events

#### 19.4.1 Reporting adverse events

AEs will be recorded in the eCRF and subject source record beginning from the time written consent/assent is provided through the follow-up visit (7 days after the last dose of study drug). Required information will be detailed in the eCRF Completion Guidelines.

#### 19.4.2 Reporting Serious Adverse Events - amended

Serious adverse events must be documented and reported to Amicus within **24 h of any study personnel knowledge of the events**. Serious adverse event reports must be faxed to the designated safety fax number (see below) to ensure appropriate dissemination and processing of the information. An alternate email address is provided as a backup, if the fax transmission is unsuccessful.

SAE FAX number: [name]

If the primary method fails, please use email: [[contact]](mailto:[contact])

Serious adverse event forms should be as complete as possible, with all known information at the time. All relevant supporting documentation (e.g., admission and progress notes, results of diagnostic evaluations/procedures/examinations, etc) available at the time of reporting should be included in the fax (or email, if necessary) along with the SAE report form. All supporting documents must be thoroughly reviewed and de-identified in accordance with local data privacy regulations prior to sending to Amicus. The subject's study number must be included

 Fax number changed via Amendment 1

 Email address changed via Amendment 1

|  |  |                    |                |
|--|--|--------------------|----------------|
|  |  | CRS Study No.:     | 090/18-03.MT   |
|  |  | Sponsor Study No.: | AT1001-035     |
|  |  | EudraCT No.:       | 2018-003684-57 |

on each page of a fax or noted in the subject line or body of an email. Reporting timelines (as described above) must not be delayed while obtaining or preparing supporting information.

If more than 1 SAE is identified in a subject simultaneously, separate SAE reports should be generated for each event.

Information not available at the time of the initial report (e.g., event end date and outcome, discharge summary, etc.) must be faxed (or emailed, if necessary) within **24 h of any study personnel knowledge of the information**. All supporting documents must be thoroughly reviewed and de-identified in accordance with local data privacy regulations prior to sending to Amicus. The subject's study number must be included on each page of the fax or in the subject line of the email.

Medical history, concomitant medication, and AE information obtained through SAE reporting must also be recorded in the eCRF.

#### **19.4.3 Additional Reporting Requirements for Suspected Unexpected Serious Adverse Reactions**

Amicus is responsible for processing suspected unexpected serious adverse reactions (SUSARs). SUSARs are also referred to as alert reports, expedited safety reports, and IND safety reports.

A SUSAR is defined as any SAE that is determined to be associated with the use of study drug and is unexpected (not currently listed in the safety reference information [see migalastat IB] or is not listed at the specificity or severity that has been observed). Amicus will notify all investigators currently conducting migalastat clinical studies of all SUSARs in accordance with applicable regulations. Suspected unexpected serious adverse reactions will be reported to the regulatory authority and IEC according to the rules in effect in each country where study sites are located:

- If the SUSAR is fatal or life-threatening, regulatory authorities and ethics committees will be notified within 7 calendar days after Amicus learns of the event.
- If the SUSAR is not fatal or life-threatening, regulatory authorities and ethics committees will be notified within 15 calendar days after Amicus learns of the event.

These notifications will need to be filed in the site's Study File Notebook and submitted to the site's IEC in accordance with policy.

Safety updates will be provided periodically to the regulatory authority and IEC responsible for the study according to the rules in effect in Germany. These updates will include information on SUSARs and other relevant safety findings.

|  |  |                    |                |
|--|--|--------------------|----------------|
|  |  | CRS Study No.:     | 090/18-03.MT   |
|  |  | Sponsor Study No.: | AT1001-035     |
|  |  | EudraCT No.:       | 2018-003684-57 |

## 19.5 Other reporting situations

### 19.5.1 Pregnancy

Pregnancy information for female subjects and female partners of male subjects participating in the study is collected by Amicus. Pregnancy in and of itself is not regarded as an AE (unless there is a suspicion that study drug may have interfered with the effectiveness of a contraceptive medication).

If a female subject becomes pregnant during the course of the study, or if the female partner of a male subject becomes pregnant during the subject's participation in the study, Amicus must be informed within 5 working days of any study staff knowledge of the pregnancy. If an SAE occurs in conjunction with the pregnancy, the SAE must be reported as described in [Section 19.4.2](#). Amicus will provide pregnancy report forms and instructions to study personnel regarding collection of pregnancy and outcome information (subject to receipt of data privacy release approvals where required under local privacy laws). Pregnancy report forms must be faxed (or emailed, if necessary) to the designated safety fax number (or email address) (see [Section 19.4.2](#)), to ensure appropriate dissemination and processing of the information.

### 19.5.2 Medication errors, including overdose

Medication error refers to any unintended error in the dispensing or administration of a study drug.

Overdose refers to administration of a quantity given per administration or given per time period that is above its maximum recommended dose.

Medication errors, including overdose, should be captured in the source document and entered into the appropriate page of the eCRFs. If a medication error is associated with AEs or SAEs, AE/SAE reporting requirements are to be followed ([Section 19.4.1](#) and [Section 19.4.2](#), respectively).

### 19.5.3 Reporting of possible study drug product quality defects

Any defect or possible defect associated with the study drug must be reported to Amicus ([[contact]](mailto:[contact])) within 1 working day of any study personnel knowledge of the possible defect. The study drug and packaging components in question, if available, must be segregated and stored in a secure area at the site under the specified storage conditions until it is determined whether or not the study drug and/or packaging is required for investigation of the possible defect. If the possible defect is associated with an SAE, the SAE must be reported as described in [Section 19.4.2](#). The SAE report must include the possible study drug defect complaint.
